### Statistical analysis

The primary analysis (primary outcome 24-hour ABPM SBP at 12 months) will use linear regression to compare 24-hour ABPM SBP between SARS-CoV-2 positive and SARS-CoV-2 negative subjects with adjustment for covariates including age, sex and BMI. The adjusted mean difference, with a 95% CI and associated p value, will be reported.

Secondary analyses will extend this regression model to examine the impact of baseline patient characteristics, and to investigate the possibility of interactions with COVID-19 clinical status. For longitudinal analysis we shall use linear mixed models as appropriate to compare changes in the mean 24-hour ABPM SBP between SARS-CoV-2 positive and SARS-CoV-2 negative subjects with adjustment for baseline 24-hour ABPM SBP and baseline covariates.

All statistical analyses will be performed using R Software V.4.0.2 or later.

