**Methods and analysis:**

The LOCHINVAR study is an observational clinical phenotyping study comparing longitudinal BP change between individuals with and without COVID-19 infection. 150 participants (30–60 years) with no history of hypertension and not on BP lowering medications will be recruited to the study to attend three visits (baseline, 12 months, 18 months). Cases will be patients who were admitted to the Queen Elizabeth University Hospital (QEUH), Glasgow, UK, with suspected/confirmed COVID-19 until 31 December 2021 and who were alive at discharge. Controls will be those who have never had confirmed COVID-19 infection. All participants will undergo clinical and vascular phenotyping studies which will include 24-hour ambulatory BP monitoring systolic BP (ABPM SBP), brachial flow-mediated dilatation urine and blood samples to assess the renin-angiotensin system, vascular inflammation and immune status. The primary outcome is the change in systolic 24-hour ABPM (ABPM SBP) between the cases and controls. Sample size was calculated to detect a mean difference of 5 mm Hg ABPM SBP at 80% power.

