Prior studies on the relationship between COVID-19 and the cardiovascular system are limited by case selection and retrospective data collection. A prospective pilot study ‘COVID-19 BP endothelium interaction study’ (ClinicalTrials.gov NCT04409847, funded by the Chief Scientific Office)^5^ compared 12-week postdischarge ambulatory BP measurements in non-hypertensive patients discharged from hospital after an admission with COVID-19 or a non-COVID diagnosis. This study showed that non-hypertensive COVID-19 patients had an 8.6 mm Hg higher 24-hour systolic BP (SBP) at 12 weeks postdischarge compared with those that did not have COVID-19 infection. A definitive prospective study with longer follow-up is required to confirm if BP is higher in post-COVID-19 patients and whether the higher BP is sustained over a longer period. The LOnger-term effects of SARS-CoV-2 INfection on blood Vessels And blood pRessure (LOCHINVAR) study is designed to answer this question along with pathophysiological studies through deep vascular phenotyping and biomarker studies of endothelial function and vascular injury. The LOCHINVAR study will help generate crucial evidence on the long-term impact of COVID-19 on BP and with information from our mechanistic studies which will facilitate the prioritisation of targetable molecular pathways that can rapidly progress into potential therapies and clinical trials.^6^

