### Study participants, screening and recruitment

The study design, study visit schedule and inclusion/exclusion criteria is shown in figure 1. One hundred and fifty participants aged between 30 and 60 years in the National Health Service (NHS) Greater Glasgow and Clyde health board catchment area, will be invited to take part in the study to attend three study visits (baseline, 12 months and 18 months). Patients, who do not have a history of high BP or hypertension treatment, admitted through the QEUH immediate assessment unit and acute receiving units with suspected/confirmed COVID-19 between 1 September 2020 and 31 December 2021 will be invited after at least 12 weeks postdischarge. The clinical criteria for clinically suspected COVID-19 include either fever, new-onset cough and/or anosmia/dysgeusia and/or ≥2 of the following presenting features: fatigue/generalised weakness, headache, myalgia, sore throat/coryzal symptoms, breathlessness, anorexia/nausea/vomiting, diarrhoea, contact with known COVID-19 positive case. Patients who are SARS-CoV-2 RT-PCR positive and/or have diagnostic chest X-ray or CT features of COVID-19 will be classified as cases.

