**Figure 1 F1:**
[figure not shown]
Study design, inclusion and exclusion criteria and study procedures. ABPM, ambulatory blood pressure monitoring; AF, atrial fibrillation; BMI, body mass index; BP, blood pressure; eGFR, estimated glomerular filtration rate; IAU, Immediate Admissions Unit. NSAID, non-steroidal anti-inflammatory drugs; OBELIX, COVID-19 blood pressure endothelium interaction study; QEUH, Queen Elizabeth University Hospital Glasgow; SBP, systolic blood pressure.

Control participants will be recruited from hospital admission records or through advertisement. Control patients recruited from hospital admission records will have an admission with COVID-19 like symptoms but are SARS-CoV-2 RT-PCR negative and have chest X-ray or CT (if performed during the relevant admission) that show low probability of COVID-19 and are SARS-CoV-2 IgG antibody negative at enrolment.

Controls recruited through advertising should have had no history of SARS-CoV-2 infection or have had a negative RT-PCR test previously and should have a negative SARS-CoV-2 IgG antibody test at enrolment. Controls will be matched for age, sex and diabetes status with cases by review of demographics of recruited cases and controls at 3 monthly intervals.

OBELIX participants have consented to be recontacted and will be invited to take part in the 12-month and 18-month follow-up visits in the LOCHINVAR study.

Screening for eligibility of all potential participants will be carried out by a member of the study team through review the electronic health record and electronic prescribing records or questionnaire responses. All participants identified as potentially eligible based on the inclusion criteria will be given a participant information sheet for the study containing contact details for the study team and given sufficient time to consider taking part. If the participant is interested, they will contact a member of the study team to discuss further and if they confirm interest in participating in the study, they will provide written, informed consent. Participants may withdraw from the study at any time.

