### Sample size calculation

From the OBELIX pilot study, we have established that ABPM SBP is normally distributed with a SD of 10 mm Hg. A mean difference of 5 mm Hg ABPM SBP between groups was determined to be the minimum clinically relevant difference. We will require 64 COVID-19 cases and 64 non-COVID control subjects to reject the null hypothesis with an alpha=0.05% and 80% power. The study requires a total of 150 subjects to be recruited (128 completed subjects) after accounting for approximately 15% missing data and ABPM errors (typical for ABPM studies). OBELIX has recruited 48 subjects and these participants will be invited into LOCHINVAR. The LOCHINVAR study will recruit the remaining subjects.

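### The secondary longitudinal model adjusts SBP change for a baseline measured after COVID-19, so a stable gap between groups can appear as a further rise in cases

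*Protocol article*

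**What the plan says.** All references are to the protocol article.

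- **Model.** Under Statistical analysis, the longitudinal data are to be analysed by mixed models whose exact form is left open. Their stated aim: "compare changes in the mean 24-hour ABPM SBP between SARS-CoV-2 positive and SARS-CoV-2 negative subjects with adjustment for baseline 24-hour ABPM SBP". Other baseline covariates are adjusted for as well. This is listed with the secondary analyses. The primary analysis is a separate linear regression of 24-hour SBP at 12 months. The covariates named for it are age, sex and BMI, and baseline SBP is not among them.
- **Timing of baseline.** Cases "will be invited after at least 12 weeks postdischarge" (Study participants, screening and recruitment). Follow-up visits are at 12 and 18 months.
- **Expected gap at that time.** The Introduction reports from the pilot that "non-hypertensive COVID-19 patients had an 8.6 mm Hg higher 24-hour systolic BP (SBP) at 12 weeks postdischarge" compared with patients without COVID-19.
- **Comparability of groups.** The abstract calls this an "observational clinical phenotyping study comparing longitudinal BP change between individuals with and without COVID-19 infection". In the text after Figure 1, "Controls will be matched for age, sex and diabetes status with cases". SBP is not a matching factor.
- **Question.** The Introduction asks whether BP is higher after COVID-19 and "whether the higher BP is sustained over a longer period".

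**The concern.** Adjusting change for baseline is sound when the groups have the same expected baseline, as after randomisation. Here the groups are defined by an exposure that precedes baseline, and the study's hypothesis is that this exposure has already raised SBP by then. Baseline SBP is therefore partly an outcome of the exposure.

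Suppose a case and a control have the same baseline SBP. If cases run higher on average, that case is low for its group and that control is high for its group. At follow-up each regresses towards its own group mean, the case upwards and the control downwards. The adjusted group term picks this up as a difference in change even when neither group mean has moved (Lord's paradox). A larger sample does not remove it.

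At stake is the study's statement about the course of SBP over time. A stable gap could be reported as progressive hypertension after COVID-19, and a partial recovery could be reported as no change.

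**Working it through.** **The plan's own figure first.** Sample size calculation states that "ABPM SBP is normally distributed with a SD of 10 mm Hg" and sets a minimum relevant difference of 5 mm Hg. With two-sided alpha 0.05 and 80% power, n per group = 2 × (1.96 + 0.84)² × 10² / 5² = 62.7, so 63. The t-test version gives 63.8, so 64, as stated. Power at 64 per group is 0.81. The stated number therefore reproduces with alpha 0.05.

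**Inputs for the check**

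- SD 10 mm Hg and 64 per group (Sample size calculation).
- Baseline gap d = 8.6 mm Hg (pilot result, Introduction) or d = 5 mm Hg (planning difference).
- Within-group correlation rho between baseline and follow-up SBP: not in the document, so assumed from 0.5 to 0.9.
- Equal SDs at each visit (assumption), so the within-group slope of follow-up on baseline is rho.

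**Step 1: what the group term estimates.**

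Adjusted group term = (follow-up gap) − rho × (baseline gap) = (true difference in change) + (1 − rho) × (baseline gap).

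The result is the same whether the outcome is follow-up or change. With a constant gap d the true difference in change is 0, and the term equals (1 − rho) × d.

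**Step 2: how often it is significant with one follow-up.**

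SE = 10 × √(1 − rho²) × √(2/64) × √(1 + (d/10)²/4), where the last factor reflects the baseline imbalance.

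Example, d = 8.6 and rho = 0.7: bias = 0.3 × 8.6 = 2.58; SE = 10 × 0.714 × 0.177 × 1.089 = 1.37; ratio 1.88; P(significant) = Φ(1.88 − 1.96) = 0.47.

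| rho | d = 8.6: false rise, mm Hg | significant | d = 5: false rise, mm Hg | significant |
|---|---|---|---|---|
| 0.5 | 4.3 | 73% | 2.5 | 35% |
| 0.7 | 2.6 | 47% | 1.5 | 21% |
| 0.8 | 1.7 | 32% | 1.0 | 15% |
| 0.9 | 0.9 | 18% | 0.5 | 10% |

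The nominal rate is 5%. A simulation of this regression (10,000 replicates per setting) agreed within 2 percentage points. The unadjusted comparison of change was significant in about 5% of replicates throughout.

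**Step 3: both follow-ups.** If the two follow-ups are averaged and all correlations equal rho, the residual SD is 10 × √[(1 − rho)(1 + 2 rho)/2]. At rho = 0.7 this is 10 × √(0.3 × 2.4/2) = 6.0. The SE becomes 6.0 × 0.177 × 1.089 = 1.15 for d = 8.6 and 6.0 × 0.177 × 1.031 = 1.09 for d = 5. The bias is unchanged, and the rejection rates rise to about 61% and 28%.

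**Step 4: a true decline.** At rho = 0.7, suppose the gap falls from 8.6 to 6.0 mm Hg. The adjusted term is 6.0 − 0.7 × 8.6 = 6.0 − 6.02, which is about 0. A narrowing of 2.6 mm Hg would be reported as none.

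**Step 5: the other model form.** If baseline, 12- and 18-month values are all outcomes and the group-by-visit term is read, simulated estimates of that term were identical with and without the baseline covariate on complete data. Over 100 replicates per setting they averaged −0.27 to +0.09 mm Hg.

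**The case against.** Four points on the other side carry weight.

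- **The text does not fully fix the model.** It leaves the mixed model to be chosen as appropriate. It does not say whether baseline is also an outcome or which coefficient is read. If all visits are outcomes and group-by-visit is the contrast, the covariate does no harm (step 5). This stands. A reader might infer that the planned analysis must report a false progression, and the document does not support that. It supports only that the most natural reading of the sentence has this fault.
- **The main result is not touched.** A reader might also infer that the study's answer on persistence is biased, particularly because the abstract words the primary outcome as a change. The Primary outcome and Statistical analysis sections define a level comparison at 12 months with no baseline SBP covariate named. It can show whether a gap is still present at 12 months. This stands, and it lowers the severity.
- **The sizes are conditional.** Rho is assumed. The 8.6 mm Hg comes from a pilot that recruited 48 subjects, and the baseline visit may fall later than 12 weeks after discharge, when the gap could differ. The table's rates are for one follow-up, whereas the plan has two. The direction stands for any rho below 1 and any positive gap, but no single rate should be quoted as this study's error rate.
- **Change given baseline is a legitimate quantity.** It is the expected difference between a case and a control who start at the same SBP. That is true, but it is not the difference in change between the groups, which is what the sentence sets out to compare. The unadjusted contrast has its own assumption: to attribute it to COVID-19, the groups must otherwise have changed in parallel.

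**Conclusion.** The concern holds for the secondary longitudinal analysis, and the plan should be corrected there. The document itself shows that baseline follows the exposure, that cases are expected to be higher at that time, and that change will be compared with adjustment for that baseline.

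Read as a difference in change, the adjusted group term is biased upwards in cases by (1 − rho) times the baseline gap. Across the assumed range of rho this amounts to between about 0.5 mm Hg (gap 5, rho 0.9) and 4.3 mm Hg (gap 8.6, rho 0.5). At the upper end it approaches the 5 mm Hg that the study treats as clinically relevant.

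The conclusion rests on equal SDs across visits, an assumed rho, a gap that persists, and the reading in which the baseline-conditional group term is interpreted as change. It does not extend to the 12-month primary regression, the sample size or the data collection.

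**What to change.** Rewrite the longitudinal sentence under Statistical analysis:

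- Remove baseline 24-hour SBP as a covariate in the analysis of change.
- Fit one linear mixed model with the baseline, 12-month and 18-month 24-hour SBP as outcomes, and with group, visit, group-by-visit and the other baseline covariates as fixed effects. An unstructured within-person covariance is suitable for three visits.
- Do not constrain the group means to be equal at baseline.
- Report as contrasts the level difference at each visit and the difference in change from baseline to 12 and to 18 months.

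If a comparison conditional on baseline is still wanted, label it as such and do not describe it as a difference in change.

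**Cost.** One sentence and no new data or visits. Intervals for change may be somewhat wider. For one follow-up the SE of the unadjusted change contrast is 10 × √(2(1 − rho)) × √(2/64). At rho = 0.5 this is 1.77, against 1.67 for the adjusted term with d = 8.6 and 1.58 with d = 5. At rho = 0.7 it is 1.37, against 1.37 and 1.30.

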### Study sponsorship, monitoring and audit

The study is sponsored by the NHS Greater Glasgow and Clyde and is coordinated in the Glasgow Clinical Research Facility. The study will be subject to audit by the Sponsor to ensure quality of study data and compliance with regulations. Any change in the study protocol will require an amendment which will be initiated by the chief investigator in discussion with the sponsor and will be ethically approved.

### Data collection, management and retention

All patients will be assigned a unique study identifier which will not contain any identifiable information. Patients in Scotland has a unique Community Health Index (CHI) number. Where linkage is required the key to CHI identification will be kept separate and only on an NHS computer. Data will be recoded in CASTOR EDC (www.castoredc.com) electronic case report forms (eCRF) held centrally on their ISO 27001 certified data management system. CASTOR EDC have been vendor assessed by the study sponsor NHSGGC in accordance with regulatory guidelines. CASTOR complies with all applicable laws and regulations, including ICH E6 Good Clinical Practice (GCP), 21 CFR Part 11, EU Annex 11, General Data Protection Regulation, HIPAA (US), ISO 9001 and ISO 27001. Data entry will be completed by either the study nurse, clinical fellow or an investigator. Data will be validated at the point of entry into the eCRF and can be checked by sponsor audit if required. To enable evaluations and/or audits from regulatory authorities, records will be kept, including the identity of all participating subjects (sufficient information to link records), all original signed informed consent forms, source documents, and detailed records of treatment disposition in accordance with ICH GCP and local regulations. All samples will be retained by the investigators. Data will be retained for a minimum of 20 years.

## Dissemination

An annual report will be issued to the Research Ethics Committee and to the funder (Heart Research UK).

Complete study results will be submitted for presentation at an international meeting, published in a peer-reviewed journal, and shared on social media. After publication, LOCHINVAR participants will be informed of results by letter. A lay summary will be made available to the participants who have taken part in the study and may be published on the funder, university or NHS website/newsletter.

## Data Availability

No data are available.
